### **8.3.6. Pregnancy**

For female patients, information on pregnancies will be collected after the start of study treatment and up to 7 days after last dose or longer if requested by the DSMB.

If a pregnancy is reported, the Investigator should inform the CVBF Safety Management Team within 24 hours of learning of the pregnancy.

Abnormal pregnancy outcomes (e.g., spontaneous abortion, foetal death, stillbirth, congenital anomalies, ectopic pregnancy) are considered SAEs.

### **8.3.7. Code breaking**

The randomization code can be unblinded upon written request to CCM, which retain the assignment correspondence. The date and reason that the blind was broken must be recorded in the source documentation and CRF, as applicable and referred to:

- the Investigators for emergency procedures.
- the CVBF Safety Management Team for pharmacovigilance purpose.

Individual treatment codes are kept in a secure location accessible only to designated staff in order to prevent dissemination of the treatment to personnel involved in study conduct who must remain blind.

#### **8.3.7.1. Emergency procedures**

The blinding should only be broken for valid medical or safety reasons, e.g., in case of a serious adverse event for which there is a reasonable possibility of a relatedness with the study medication (i.e., serious adverse reaction) and it is necessary for the PI or another delegated site staff member to know which treatment the patient is receiving before he/she can be properly treated for the event.

If the code is broken for an urgent safety situation, the patient will be withdrawn from the study.

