## **8.2. Discontinuation/Withdrawal Criteria**

### **8.2.1. Discontinuation of Study Treatment**

Definitive treatment discontinuation for individual subjects may occur due to undesirable effects related to the systemic use of oral IMP as follows: severe allergic reaction; serious skin conditions; serious muscle weakness, soreness, pain or breakage or change in color of the urine (rhabdomyolysis) (rare;  $\geq 1/1,000$ ); unusual bleeding or bruising, suggesting a liver disorder; Lupus-like illness syndrome (very rare;  $< 1/10,000$ ).

The SMB will evaluate further “stopping rules” or “discontinuation criteria” based on side effects registered during the trial.

All definitive treatment discontinuation reasons and dates should be recorded by the investigators in the appropriate CRF page when considered as confirmed.

The study will be stopped if any of the following are found:

- i. a death possibly/probably related to the IMP;
- ii. treatment discontinuation (> 15% patients) due to severe adverse effects (SAEs) related to the systemic use of oral IMP.

If the IMP administration is prematurely discontinued the primary reason for discontinuation must be recorded in the CRF.

See the SoA for data to be collected at the time of treatment discontinuation and follow-up and for any further evaluations that need to be completed.

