### **8.2.3. Withdrawal from the Study**

Patients will be informed that they have the right to withdraw from the study at any time (withdrawal of consent), without prejudice to their medical care, and are not obliged to state their reasons. Patients who have withdrawn consent to the study or who for any cause have discontinued the study cannot be reincluded in it. Investigators may decide to discontinue the study for a patient for any clinical problem, or if other issues arise (such as, for example, non-compliance with the Protocol, etc.).

The withdrawal or discontinuation of the patient from the Study must be documented in the CRF. If a patient fails to return to the centre for a scheduled visit, attempts should be made to contact the patient to ensure that the reason for not returning is not a SAE. Likewise, if a patient declares his/her wish to discontinue from the study e.g. for personal reasons, an attempt should be made to establish that the true reason is not a SAE (bearing in mind the patient is not obliged to state his/her reasons).

Safety laboratory tests should be performed whenever possible at patient withdrawal.

It is also possible for the study to be terminated prematurely by the Sponsor in case of:

- new information leading to an unfavorable risk-benefit assessment of the IMP, such as occurrence of previously unknown significant adverse reactions or unexpectedly high intensity or incidence of known adverse reactions, or other unfavorable safety findings;
- Trial no longer justified for clinical or ethical reasons;
- withdrawal of IMP from the market for safety reasons.
- Finally, the trial could be terminated or suspended at the request of health authorities.

If the study will suffer of more than the expected 15% of dropout, the endpoints will be calculated anyway, as a proof of principle. In case of missing data to achieve the aims, these will be imputed using multiple imputation and a sensitivity analysis will be performed on the imputed data.

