### 9.2. Populations for Analyses

The Safety population will consist of all patients who received any study medication and will be based on the treatment actually received. The Safety population will be used to present the demographic and baseline data, and all safety data.

The Intent to Treat (ITT) population will consist of all patients who are randomized and receive the IMP (either Atorvastatin or placebo); it will be based on the treatment randomized, regardless of the treatment actually received. The ITT population will be used to present efficacy data.

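### An emergency code break ends study participation and investigators may end it at their discretion, with no ECHO set out at exit, so T18 strain goes uncollected in some patients the ITT analysis counts as randomized

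*Protocol*

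**What the plan says.** Five places in the protocol bear on whether a patient who stops treatment, or whose code is opened, still has the primary endpoint measured.

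- **Section 8.3.7.1 (Emergency procedures).** The example given for opening the code is "in case of a serious adverse event for which there is a reasonable possibility of a relatedness with the study medication", where the treatment must be known to manage the event. The consequence is mandatory: "If the code is broken for an urgent safety situation, the patient will be withdrawn from the study".
- **Section 8.2.3 (Withdrawal from the Study).** "Investigators may decide to discontinue the study for a patient for any clinical problem, or if other issues arise", with the example "such as, for example, non-compliance with the Protocol, etc". Patients who withdraw consent, or who "for any cause have discontinued the study cannot be reincluded in it", are out for good. The only assessment named at exit is laboratory: "Safety laboratory tests should be performed whenever possible at patient withdrawal".
- **Section 8.2.1 (Discontinuation of Study Treatment).** "See the SoA for data to be collected at the time of treatment discontinuation and follow-up".
- **Section 2 (Schedule of Activities).** The columns are T0 (screening and randomization), T2, T4, T9, T12, T15, T18 and the month-19 call. ECHO is marked at T0, T9 and T18. No column, row or footnote covers treatment discontinuation or early exit.
- **Section 9.2 (Populations for Analyses).** The ITT population, used for efficacy, is everyone randomized who receives the IMP, and "it will be based on the treatment randomized, regardless of the treatment actually received".

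Section 9.1.4 (Missing data) settles what happens when strain is missing. Drop-outs before T9 are left out of the analysis and imputation after T9 is optional. The section expects more patients to leave the atorvastatin arm, because of adverse effects.

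**The concern.** An as-randomized analysis that ignores treatment actually taken needs outcomes from patients who have stopped treatment. Section 8.3.7.1 removes one group of them by rule, and Section 8.2.3 allows others to be removed by decision. Section 8.2.1 points to a collection scheme that the Schedule does not contain. Read together, these sections do not tell a site to obtain a T18 ECHO in such a patient, and for an emergency code break they tell it the opposite.

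The loss is not random. The example given for a code break is a serious event suspected to be drug-related, and the protocol itself expects more loss on atorvastatin for adverse effects. A patient withdrawn around the T2 or T4 safety check has no post-baseline ECHO and drops out of the comparison under Section 9.1.4.

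For the primary endpoint, little is gained by losing the measurement. Section 7.4 has ECHO read in a core laboratory by two observers blinded to assignment. Opening one patient's code at a site does not unblind them.

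**Working it through.** **1. The plan's own figures (Section 9.1).** Inputs: difference 2.4 points, SD 4.5, one-sided alpha 0.05, power 80%, 1:1 allocation.

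n per group = 2 × (1.645 + 0.842)² × (4.5 / 2.4)² = 2 × 6.18 × 3.516 ≈ 43.5, rounded up to 44. This matches the stated 44 per group, 88 in total. The stated 102 follows from 88 × 1.15 = 101.2, rounded up to an even total.

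With 15% loss, 102 × 0.85 = 86.7 patients remain, or 43.35 per group.

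**2. Effect on power (noncentral t, one-sided 0.05, 51 randomized per arm).**

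| Loss, atorvastatin / placebo | Evaluable per arm | Power |
|---|---|---|
| Planned evaluable | 44 / 44 | 79.9% |
| 15% / 15% | 43.35 / 43.35 | 79.3% |
| 20% / 10% | 40.8 / 45.9 | 79.2% |
| 25% / 5% | 38.25 / 48.45 | 78.8% |

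Unequal loss at the planned overall rate costs about one percentage point at most.

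**3. How many patients could be affected.** The protocol gives no rate of code breaks or investigator withdrawals. The nearest figures are in Section 3.3: 5.2% on atorvastatin and 4.0% on placebo discontinued for adverse reactions, over an average of 53 weeks.

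- Atorvastatin: 51 × 0.052 = 2.65.
- Placebo: 51 × 0.040 = 2.04.
- Total: 4.69 of 102; difference between arms: 0.61 patient.
- Scaled linearly to 18 months, about 78 weeks (assumption): 4.69 × 78 / 53 = 6.9.

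These counts cover stopping for adverse reactions of every kind. Emergency code breaks are only a part of them.

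**4. Size of the bias.** Assumptions: the retained atorvastatin patients show the planned 2.4 points; a fraction f of that arm is lost with true effect e between 0 and 1.2 points; losses on placebo are unrelated to outcome; the analysis uses only patients with T18 strain.

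Effect in the whole arm = 2.4 × (1 − f) + e × f. Overstatement = f × (2.4 − e).

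| f | Whole-arm effect (e = 0 to 1.2) | Overstatement (e = 1.2 to 0) |
|---|---|---|
| 5.2% (Section 3.3) | 2.28 to 2.34 | 0.06 to 0.13 |
| 10% | 2.16 to 2.28 | 0.12 to 0.24 |
| 15% | 2.04 to 2.22 | 0.18 to 0.36 |

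The first row already treats every atorvastatin patient who stops for an adverse reaction as lost. The 15% row is the worst case shown (0.36 / 2.4 = 15% of the planned effect) and would need the whole drop-out allowance in the atorvastatin arm to be of this kind.

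**The case against.** The strongest reply is that the protocol does separate these events. Treatment discontinuation, temporary discontinuation and study withdrawal have their own sections. Section 8.2.1 speaks of follow-up and further evaluations after treatment stops, and Section 9.1.4 asks investigators to encourage participation to the end of the trial. The plan also has remedies for missing data: multiple imputation with a sensitivity analysis (Section 8.2.3), imputation after T9, use of outside records, and a possible correction if drop-out proves outcome-related (Section 9.1.4).

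Much of this stands, and it rules out several stronger readings that a reader might infer:

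- **That stopping the tablet means leaving the study.** No section says so. For patients who only stop treatment, the fault is a cross-reference that leads nowhere.
- **That every unblinding forces withdrawal.** Only the urgent-safety route does. The pharmacovigilance route (Section 8.3.7.2) and the best-interest route (Section 7.4) state no withdrawal.
- **That non-adherent patients are removed, mostly from the active arm.** Section 8.2.3 is discretionary and concerns non-compliance with the protocol. Nothing ties it to tablet-taking or to one arm.
- **That the ITT analysis becomes impossible.** Section 9.2 fixes who is analysed and in which arm. It does not require complete data.
- **That a large share of the 15% drop-out allowance is lost by rule.** No figure in the protocol supports any share. Only emergency code breaks are lost by rule.

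The remedies do not answer the point that remains. None of them yields a T18 strain value read in the core laboratory, and Section 9.1.4 itself concedes that imputation rests on assumptions that cannot be tested. A separate analysis plan cannot recover an ECHO that was never taken.

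**Conclusion.** The point holds in a limited form. Mandatory withdrawal after an emergency code break, discretionary withdrawal with laboratory tests alone at exit, and a reference to a Schedule entry that does not exist together mean that T18 strain is not collected in some patients analysed as randomized. For code breaks, the loss is linked to suspected drug reactions.

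The likely size is modest. The protocol gives no count. The Section 3.3 rates suggest 4 to 5 patients stopping for adverse reactions of any kind (about 7 if scaled linearly to 18 months), only some of them through a code break. Loss of power is negligible. The bias is about 0.06 to 0.13 points at the 5.2% rate, on the assumption of a true effect of 0 to 1.2 points in lost atorvastatin patients. It should still be corrected, because the loss is avoidable, falls where it is least ignorable and is cheap to prevent.

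**What to change.** Reconcile Sections 8.2.1, 8.2.3, 8.3.7.1 and 9.2 with the Schedule of Activities:

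- State that a code break, or the end of study treatment, does not by itself end follow-up.
- State that the scheduled T9 and T18 assessments, including the core-laboratory ECHO, continue unless the patient withdraws consent to follow-up.
- Where T18 will not be attended, offer an ECHO at exit.
- Add a Schedule column or footnote saying this, so that the reference in Section 8.2.1 has a target.

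Leave every decision on stopping the IMP to the existing clinical text. This change concerns data collection only.

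The cost is protocol wording and one Schedule entry, using visits already scheduled. The downside is that some patients attend visits while off treatment. Questionnaires and patient-reported events collected after a code break may no longer be blinded, so they should be flagged in the data and in the analysis.

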#### **8.3.7.2. Pharmacovigilance purposes**

Treatment codes can only be broken by the CVBF Safety Management Team for the purpose of reporting a SUSAR to the regulatory authorities.

In the event of an SAE, the case is assessed by the Investigator for seriousness and causal relationship and by the CVBF Safety Management Team for expectedness.

If the case appears to be a SUSAR, then the blinding should be broken. It is important that the blind is being broken only for that specific patient.

Following unblinding,

- a) if the product administered to the subject is atorvastatin, the serious adverse reaction will be reported as SUSAR to the regulatory authorities;

- b) if the product administered to the subject is the placebo, the serious adverse reaction will be reassessed and if confirmed to be SUSAR (e.g., reaction due to an excipient or impurity), it will be reported to the regulatory authorities.

Suspected unexpected serious adverse reactions will be reported on expedite basis.

#### **8.4. Treatment of Overdose**

For this study, any dose of Atorvastatin greater than 240 mg within a 24-hour time period will be considered an overdose.

Decisions regarding dose interruptions or modifications will be made by the investigator in consultation with the Medical Monitor based on the clinical evaluation of the patient.

#### **8.5. Safety Assessments**

Planned time points for all safety assessments are provided in the SoA.

The most common (about 1:100) atorvastatin-related adverse reactions, based on data from clinical trials and extensive post-marketing experience are: allergic reactions, hyperglycemia, headache, pharyngolaryngeal pain, epistaxis, constipation, flatulence, dyspepsia, nausea, diarrhea, myalgia, arthralgia, pain in extremities, muscle spasms, joint swelling, back pain, abnormalities of liver function tests, increased creatine kinase, increased serum transaminases.

Uncommon (less than 1:100) adverse reactions include: loss of appetite, male gain, decreases in blood sugar levels, insomnia, dizziness, numbness or tingling in the fingers and toes, reductions of sensation to pain or touch, change in sense of taste, loss of memory, blurred vision, ringing in the ears and/or head, vomiting, belching, abdominal pain upper and lower, inflammations in pancreas or liver, skin rash and itching, hair loss, neck pain, muscle fatigue, chest pain, swelling especially in the ankles, raised temperature, urine tests that are positive for white blood cells.

Rare (1:1,000) adverse reactions include: serious allergic reaction, severe skin peeling, swelling or rash, Muscle weakness, pain, associated to red-brown discoloration of urine and high temperature (suggestive of rhabdomyolysis), visual disturbance, unexpected bleeding or bruising cholestasis (yellowing of the skin and whites of the eyes), tendon injury.

Very rare (1:10,000) adverse reactions include: Lupus-like disease syndrome (including rash, joint disorders and effects on blood cells); unexpected or unusual bleeding or bruising, suggestive of a liver complaint, hearing loss, gynecomastia.

The parameters used to ensure safety are mainly constituted by blood tests and patient reported adverse events.

Enrolled patients will be encouraged to report adverse events spontaneously even without direct questioning by the investigator. For each adverse event reported by the patient, the investigator will obtain all information and documentation necessary for an accurate description of the adverse event.

The adverse events can be reported by the patient at any time, as soon as possible during-after occurrence. Blood tests at the visits T2, T4, T9 and T18 might uncover some hidden adverse events.

All adverse events, regardless of severity, or presumed relationship to the experimental intervention or control intervention planned for the study will be recorded in the clinical record.

The record will include: level of severity, start and end date, drug correlation assessment and measures taken to address the adverse event, final outcome.

##### **8.5.1. Physical Examinations**

A brief physical examination will include assessments of the cardiovascular system and abdomen (liver and spleen). Height and weight will also be measured and recorded.

#### **8.5.2. Vital Signs**

Pulse rate and blood pressure will be assessed. Blood pressure and pulse measurements should be preceded by at least 5 minutes of rest for the participant in a quiet setting without distractions (eg, television, cell phones). In addition, physical exercise habits will be registered.

#### **8.5.3. Electrocardiograms**

12-lead ECG will be obtained as outlined in the SoA.

#### **8.5.4. Clinical Safety Laboratory Assessments**

The list of clinical laboratory tests to be performed are provided in the SoA together with the timing and frequency.

The investigator must review the laboratory report, document this review, and record any clinically relevant changes occurring during the study in the AE section of the CRF. The laboratory reports must be filed with the source documents. Clinically significant abnormal laboratory findings are those which are not associated with the underlying disease, unless judged by the investigator to be more severe than expected for the participant's condition.

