#### **8.3.1. Definitions**

##### **8.3.1.1. Adverse Event**

An Adverse Event (AE) is defined as any untoward medical occurrence in a subject to whom a medicinal product is administered and which does not necessarily have a causal relationship with this treatment.

An AE can therefore be any unfavourable and unintended sign (including an abnormal laboratory finding), symptom, or disease temporally associated with the use of a medicinal product, whether or not related to the medicinal product.

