##### **8.3.1.3. Serious Adverse Event**

A serious adverse event (SAE) is defined as any untoward medical occurrence that at any dose requires inpatient hospitalisation or prolongation of existing hospitalisation, results in persistent or significant disability or incapacity, results in a congenital anomaly or birth defect, is life-threatening, or results in death.

An important medical event that based upon appropriate medical judgment, may jeopardize the patient and may require medical or surgical intervention to prevent one of the outcomes listed above is also an SAE.

Symptoms or medically significant laboratory or instrumental (e.g., electrocardiographic) abnormalities of a pre-existing disease, such as cancer or other disease, should not be considered an adverse event. However, occurrence of new symptoms, or laboratory or instrumental abnormalities, as well as worsening of pre-existing ones, are considered adverse events. Planned procedures that require hospitalization will not be considered SAEs.

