#### **9.1.3 Analysis of safety variables**

AEs will be presented in terms of the number of AE, the incidence, severity and relationship to the study drug, overall and by body system and preferred term. SAEs will be presented in the same way.

Results for routine laboratory tests will be assessed as being below the lower limit of the normal range, within the normal range or above the upper limit of the normal range. The frequency of patients reporting an abnormal or abnormal clinically significant laboratory value at screening and follow-up will be presented for each laboratory variable. Vital signs will be presented using descriptive statistics.

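### Protocol 8.5.4 and 8.3.1.3 apply different tests to laboratory changes put down to ACM, so the same rise can be an adverse event under one and be left out under the other

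*Protocol*

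**What the plan says.** Section 8.5.4 requires the investigator to review each laboratory report and to "record any clinically relevant changes occurring during the study in the AE section of the CRF". The same paragraph then gives its only criterion: "Clinically significant abnormal laboratory findings are those which are not associated with the underlying disease, unless judged by the investigator to be more severe". The sentence carries an exception, which in full reads "unless judged by the investigator to be more severe than expected for the participant's condition".

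The AE definitions use another test. Section 8.3.1.1 includes "any unfavourable and unintended sign (including an abnormal laboratory finding), symptom, or disease temporally associated with the use of a medicinal product", and it applies "whether or not related to the medicinal product". Section 8.3.1.3 first says that abnormalities belonging to a pre-existing disease "should not be considered an adverse event". It then limits that carve-out: new abnormalities, "as well as worsening of pre-existing ones, are considered adverse events". Section 8.5 adds that all AEs are recorded irrespective of severity or presumed relationship to the study intervention. Section 8.3.2.2 makes causality a separate assessment.

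On the analysis side, Section 4 lists the number and severity of AEs, including variation in blood safety parameters, as a secondary endpoint. Section 9.1.3 classes each routine result as below, within or above the normal range, and reports how many patients have an "abnormal or abnormal clinically significant laboratory value" for each variable.

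**The concern.** A rule that decides whether a laboratory change is counted should not depend on what the investigator thinks caused it, because attribution has its own step in 8.3.2.2. In 8.5.4 presumed cause enters earlier, in the paragraph that sends laboratory changes to the AE section.

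The tests most exposed are the ones that matter for this drug. Section 8.5 names abnormal liver function tests, raised creatine kinase and raised transaminases among the most common atorvastatin reactions, and says that safety rests mainly on blood tests and patient reports. Section 8.5.6 lists CK, AST/ALT and LDH together with troponin and NT-proBNP in one panel of safety and disease-progression markers, to be measured by the centres' own laboratories. Attribution to ACM is therefore a choice a site could make, and two sites could make it differently.

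At stake are the consistency of the AE counts across sites and the content of the clinically significant category.

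**Working it through.** No arithmetic applies: the point turns on wording, and the protocol states no rate of laboratory abnormalities and no rate of attribution to ACM. The check is to take each kind of laboratory finding through both rules.

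| Finding | 8.3.1.3: an AE? | 8.5.4: clinically significant? | Agree? |
|---|---|---|---|
| Abnormality of existing disease, unchanged | No | No, if of expected severity | Yes |
| New or worsened, not attributed to ACM | Yes | Yes | Yes |
| New or worsened, attributed to ACM, worse than expected | Yes | Yes, by the exception | Yes |
| New or worsened, attributed to ACM, of expected severity | Yes | No | **No** |

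The rules conflict in the last row only. Worsening is judged against the patient's own earlier values. Severity beyond expectation is judged against what the investigator anticipated for that patient. In a progressive disease a change can be a worsening and still be anticipated.

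Section 8.3.5 does not resolve this row. Its list of disease-related events kept out of expedited SAE reporting has four clinical entries (cardiac-arrest death, ICD intervention for VT, cardiac syncope and heart-failure hospitalisation) and no laboratory finding.

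Where a last-row finding would appear in the results:

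- **AE counts (Section 4, 9.1.3).** Present if the site follows 8.3.1.3, possibly absent if it takes 8.5.4 as its guide.
- **Clinically significant category (9.1.3).** Absent under the definition in 8.5.4.
- **Abnormal category (9.1.3).** Present, because it depends only on the reference range.
- **Variation in blood safety parameters (Section 4).** Present, because it uses the measured values.

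The abnormal category has one gap. Section 6.2 excludes CK, and persistent transaminase elevation, only above 3 times the upper limit of normal, so a patient may enter already above normal. If that patient's value rises further, it is classed as above the range at screening and at follow-up, and the range table shows no change. Within the tables of 9.1.3 only the clinically significant category could show that worsening, and that is the category 8.5.4 ties to presumed cause.

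**The case against.** The strongest reply is that 8.5.4 defines clinical significance, not an adverse event, and that nothing in it cancels the general duty in 8.3.2 and 8.5 to record all AEs. This stands in part. It is why such a finding may, rather than will, go unrecorded. But 8.5.4 speaks of clinically relevant changes in its recording duty and of clinically significant findings in its definition, without saying whether these are the same. A site could reasonably read the second as explaining the first.

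A reader might also infer more than the protocol supports:

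- **That any finding linked to ACM is barred from being clinically significant.** It is not. The same sentence brings back findings judged worse than expected, and a marked rise on treatment could well qualify.
- **That drug-related rises disappear from view.** They do not. Section 9.1.3 tabulates every out-of-range value regardless of cause, and Section 4 includes variation in the blood safety parameters.
- **That 8.5.4 contradicts the AE definition as a whole.** Section 8.3.1.3 has its own carve-out for existing disease, and the two sections agree in three of the four situations above.
- **That blinded judgement is the fault.** Blinding (7.4) keeps attribution from depending on known allocation. If the same fraction f of findings were put down to ACM in both arms, the observed rates would be p1(1 − f) and p0(1 − f). The ratio p1/p0 would be unchanged and the difference would shrink by the factor (1 − f). The documents give no value for p1, p0 or f, so no size can be attached.

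It is also fair to say that the protocol nowhere states that ACM raises CK or transaminases. How often investigators would make that attribution is unknown.

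**Conclusion.** The mismatch is real, narrow and minor. It concerns new or worsened laboratory abnormalities that are attributed to ACM and judged of expected severity. These are AEs under 8.3.1.3 but not clinically significant under 8.5.4. The exposure is limited to the AE counts and the clinically significant category, and to differences between sites in how they count. All out-of-range values remain in the laboratory tables.

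This rests on two assumptions: that some investigators will attribute liver or muscle test rises to ACM, and that some will take 8.5.4 as the test for what goes into the AE section. The protocol allows both but does not show how often either would happen. It is worth correcting because the correction is cheap, AE number and severity are a secondary endpoint, and these tests are where atorvastatin effects are expected.

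**What to change.** Reconcile 8.5.4 with 8.3.1.1, 8.3.1.3 and the recording rule in 8.5:

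1. State in 8.5.4 that a new laboratory abnormality, or worsening of an existing one, is recorded as an AE whatever its presumed cause.
2. Remove association with the underlying disease as a condition of clinical significance. Define the term without reference to cause, for example by the value itself or by the action or follow-up it leads to.
3. Use one term, relevant or significant, for the recording duty and for the category in 9.1.3.
4. Keep attribution to ACM or to the study drug in the relatedness assessment of 8.3.2.2.

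The cost is a wording amendment and a short note to sites. The downside is somewhat more laboratory AEs recorded in both arms, some of which will reflect the disease. The relatedness field is where the investigator's view on that is recorded.
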